### 2.4. Study Procedure

The intervention group will be provided with 16 weeks of intensive, hands-on culinary and lifestyle skills instruction (2 in-person and 14 virtual), followed by 6 monthly, virtual classes. Intervention and control group participants will be assessed at baseline, 4 months, 12 months, and 18 months. Control group participants will be provided with 2 in-person and 14 recorded videos of intervention classes after the 12-month assessment timepoint. See Table 2 for assessment timetable. Enrollment began in August 2023 and all participant study activities will end in October 2025.

#### 2.4.1. TK-MT Intervention

The 12-month TK-MT intervention program will be delivered by a culinary educator, a registered dietitian, and behavioral/lifestyle experts with health coaching and motivational interview training. There will be a minimum of two instructors facilitating each class; facilitator roles may change throughout intervention. The first 2 in-person classes will be held at academic or community-based teaching kitchens affiliated with each study site. For subsequent classes, participants will join via a video conferencing platform and cook in their home kitchens while facilitators lead from a teaching kitchen. The first 16 core classes (classes 1–16) will be held weekly and last approximately 2 h. The remaining 8 booster classes (classes 17–24) will be held monthly and last approximately 2 h. RAs trained in intervention implementation will be present during classes to assist participants. An overview of the TK-MT educational intervention is detailed in Table 3.

##### TK-MT Intervention Curriculum

The TK-MT curriculum is grounded in the social cognitive theory (SCT), which emphasizes the impact of behavioral capability, self-efficacy, and social influences on shaping health behaviors [45]. The curriculum combines observational learning through live modeling demonstrations with hands-on practice and skill-building activities in cooking, nutrition and food literacy, mindfulness, and physical activity. Participants observe instructors and peers, gaining cooking knowledge, skills, and self-efficacy to replicate these behaviors on their own. The TK-MT curriculum fosters self-efficacy by providing opportunities for mastery experiences. Participants receive ongoing feedback, troubleshoot challenges, and gain positive reinforcement as they learn and practice new skills. Successfully planning, preparing, and enjoying healthy meals strengthens their belief in maintaining these behaviors over time. The TK-MT curriculum also fosters a sense of community and social support. Through group discussions and activities, participants learn from and motivate each other. This social interaction builds a support network that can reinforce healthy habits beyond the program duration. By integrating these SCT principles, the TK-MT curriculum seeks to empower participants with the knowledge, self-efficacy, and social support needed to make lasting changes that contribute to a healthier lifestyle.

The TK-MT curriculum is based on the Harvard Healthy Eating Plate [46] and the Substance Abuse and Mental Health Services Administration’s (SAMHSA) Wellness Initiative [47]. The Harvard Healthy Eating Plate emphasizes the importance of consuming a high-quality, diverse diet that is rich in healthy carbohydrates, low in sugary beverages, and incorporates heart-healthy oils [46]. (An overview of the curriculum content can be found in Appendix B). The SAMHSA Wellness Initiative frames wellness as an interconnected, complex concept that functions across 8 different dimensions: emotional, physical, occupational, intellectual, financial, social, environmental, and spiritual [47]. The details of the culinary, nutrition, and lifestyle curriculum components were outlined by the TKC expert multi-day meetings (Appendix C). Mindfulness, physical activity, and behavior change (e.g., goal setting) exercises come from TKC members trained as health coaches and exercise specialists.

##### Grocery Acquisition

Sites will vary in methods used to provide study participants with their groceries to help compare and determine which practice would be the best fit for future replication. Sites may use grocery delivery to participant homes, curb-side pick-up at grocery stores, or pick-up at the study site for recipe ingredients needed for class participation. Sites will determine their method based on factors such as availability of delivery services, travel complexity, and staff availability for grocery bag assembly and distribution. Each study site will document their method of grocery acquisition along with resource requirements (food cost, labor cost, time, site level capacity).

#### 2.4.2. Usual Care (Wait-List Control Group)

Participants randomized to the wait-list control group will receive standard care (as defined by their primary care physician) for 12 months and will be offered the opportunity to participate in an abbreviated version of the TK-MT intervention following the 12-month assessment period. This version will include two in-person classes to gain practical hands-on cooking experience, educational handouts and recipes from the full 12-month TK-MT program, access to the study website, and audiovisual recordings of classes 3–16. The control group will not receive grocery ingredients to prepare the recipes in the program. At the 18-month assessment timepoint, control group participants will be sent a REDCap survey via email to assess usability, satisfaction, and overall experience of the abbreviated TK-MT intervention.

### 2.5. Outcome Measures and Data Collection

Sociodemographic data such as age, gender, race, ethnicity, income, and education, along with reasons for participation, will be collected at baseline from all participants via an online REDCap survey. Food security will also be assessed at baseline using the Hunger Vital Sign screener along with questions asking about types of food assistance received and distance to the closest grocery store. In addition, study staff will collect participants’ current medication information via a video or phone call at baseline as part of eligibility screening and enter the information into the REDCap medication form.

Self-reported medications will be reviewed during the 4-, 12-, and 18-month follow-up assessment points to assess dosage changes over the course of the study; medication changes will be treated as confounders as well as considered as independent outcomes of the teaching kitchen intervention. Given the length of this study, participants in both arms will be encouraged to receive ongoing care from their primary care physician, including medication management as appropriate.

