#### 2.3.3. Recruitment and Randomization

Potential participants will be recruited through the TK-MT website, paid social media advertisements, physical and digital flyers, social media postings, institutional emails, television spots, ads in community newspapers, booths at health fairs, and referrals from research or clinical staff at the study sites. Study recruitment will follow the process outlined in Figure 1. Preliminary study eligibility will be assessed through an optional pre-screening survey on the TK-MT website followed by a screening phone call.

Alternatively, interested individuals can call the study team directly and complete a phone call screening. Those who are likely eligible based on the phone call screening will complete a follow-up video call with a trained research assistant (RA). These screening methods will collect eligibility data and visually confirm minimal operating kitchen equipment described in the inclusion criteria. The RA will explain the study details and obtain informed consent during these screening calls. Final eligibility will be confirmed by study site PI based on a review of anthropometric data, laboratory data, self-reported medication lists, and study site MD recommendations.

Eligible participants will be randomized at the site level in blocks to either the TK-MT intervention group or the wait-list control group receiving standard care (i.e., followed as usual by their primary care physician). Each site will independently enroll 1–2 cohorts and randomize 28–48 participants to each study arm (for single-cohort sites) or 14–30 participants per arm (for double-cohort sites); the wait-list control group will receive a condensed version of the intervention curriculum after completing the 12-month assessments. Individuals who share a household can participate in this study only if they have separate kitchen workspaces for virtual classes and must be randomized to the same study arm. All recruitment and randomization data will be documented in site-specific REDCap surveys and forms. Incentives, in the form of gift cards and small gifts (notepad, measuring spoons, etc.) valued at a total of USD 200 per individual will be provided after completing (1) laboratory and anthropometric screening, (2) baseline psychometric assessments, (3) 4-month assessments, (4) 12-month assessments, and (5) 18-month assessments.

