##### Laboratory Data

Fasting blood glucose, fasting insulin, hemoglobin A1c, ALT, and AST (collected as a hepatic panel), and fasting lipid profile (total cholesterol, triglycerides, HDL, and LDL) will be collected by venipuncture at baseline, 4, 12, and 18 months. Data will be collected at affiliated or at independent laboratories. All laboratory data collections will be conducted according to SOPs regardless of study site or collection location. Once lab results are received by the study team, staff will enter the data into the REDCap laboratory data form (see Table 5), which will be reviewed by the site medical director. Participants will be notified of any concerning values and given a letter to discuss with their primary provider. Study teams will assist in this communication (see Table 5).

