### 2.7. Data Analysis

The primary outcome of feasibility will be assessed through frequency data that are collected on recruitment, attendance, and fidelity. Descriptive statistics (proportions for rates, means, or medians for satisfaction scores) will be used to summarize these measures. We will also document reasons for non-completion (withdrawal or attrition). For surveys addressing participant satisfaction, descriptive statistics (means, medians, proportions, 95% confidence intervals [CI]) will be computed, and data will be analyzed to assess for change over the 16-week intensive curriculum, 8-month boosters, and 18-month sustainability measures. A paired *t*-test will evaluate pre/post changes in continuous measures. 

Secondary associations considering participation in the TK-MT and the biometric data (change in body weight and clinically relevant change in one of the following metabolic markers: fasting plasma concentrations of glucose, insulin, triglyceride, cholesterol, HDL, LDL, and liver function as AST and ALT) will be analyzed using a linear mixed-effects regression model for continuous outcomes. 

Descriptive statistics (means, medians, proportions) will be used to summarize baseline characteristics and changes in these outcomes (self-reported health behaviors, lab values, and anthropometrics) over time. Baseline and demographic data will be controlled for in this model. Lastly, we will investigate whether missing data, due to dropouts and poor attendance, are non-ignorable through a sensitivity analysis based on the imputation approach developed by co-investigator [name] and colleagues [65]. Preliminary investigation of associations and correlations will be explored graphically and formally using parametric and nonparametric tests, as appropriate. Regression diagnostics will be performed to assess the validity of the multivariate models and their assumptions, and first-order interaction terms will be included to assess potential effect modification. 

For participant interviews and open-ended survey items, thematic analysis will be conducted by the HSPH team to independently read transcripts and conduct open and then focused coding using inductive and deductive coding approaches in NVivo (15, Lumivero, Denver, CO, USA) [66].

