## Appendix A

The target study population is 320 participants based on the capacity of a teaching kitchen (20 study participants in the TK arm and 20 in the control group times two cohorts at each of four sites). Power calculations using a total sample size of 320 participants indicate that the teaching kitchen intervention is designed to detect a significant improvement in metabolic syndrome biomarkers, with an improvement rate of approximately 31.8% needed in the intervention group to demonstrate a meaningful effect compared to the control group.

Improvement in at least one of the following metabolic markers (fasting plasma concentrations of glucose, insulin, ALT/AST, and lipids including cholesterol, triglycerides, LDL, HDL, and cholesterol HDL cholesterol ratio or the triglyceride HDL cholesterol ratio) after participation in our TK intervention.

Given that:

- There are two arms: control group and intervention group.
- Total sample size is 320.
- Two-sided test.
- Under a significance level of 0.05.

Assume that the percentage of improved study population in the control group is ranging between 5% and 15%.

**Table A1 nutrients-17-00314-t0A1:** Test: Two-Sample Proportional Test.

Assumed Prevalence in Control Group	Proportion Randomized to the Intervention Arm	Minimum Detectable RELATIVE Risk *		Percentage of Improved Study Population in Intervention Group	
		Power = 0.8	Power = 0.9	Power = 0.8	Power = 0.9
5%	0.3	2.95	3.39	14.75%	16.95%
	0.5	2.84	3.21	14.20%	16.05%
	0.7	3.14	3.52	15.70%	17.60%
10%	0.3	2.22	2.46	22.20%	24.60%
	0.5	2.14	2.35	21.40%	23.50%
	0.7	2.29	2.51	22.90%	25.10%
15%	0.3	1.92	2.09	28.80%	31.35%
	0.5	1.86	2.01	27.90%	30.15%
	0.7	1.96	2.12	29.40%	31.80%

Assumed prevalence is the percentage of improved study population; * the ratio of prevalence in the intervention arm over that in the control arm; calculations based on effect estimates as reported in Effectiveness of a Lifestyle Intervention on Metabolic Syndrome. A randomized controlled trial [44].

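### Section 2.5 gives post-randomisation medication changes the role of confounder as well as outcome; the main arm comparison should not condition on them, and sections 2.5 and 2.7 need reconciling

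*Protocol article*

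**What the plan says.** Four statements in the protocol article bear on this.

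- **Design (2.3.3).** The comparison is randomised: "Eligible participants will be randomized at the site level in blocks to either the TK-MT intervention group or the wait-list control group".
- **Medication (2.5).** Medication is recorded at baseline. After that, "Self-reported medications will be reviewed during the 4-, 12-, and 18-month follow-up assessment points to assess dosage changes". The plan then assigns the variable its roles: "medication changes will be treated as confounders as well as considered as independent outcomes of the teaching kitchen intervention". It adds that "participants in both arms will be encouraged to receive ongoing care from their primary care physician, including medication management as appropriate".
- **Laboratory results (Laboratory Data).** Out-of-range results feed back to usual care: "Participants will be notified of any concerning values and given a letter to discuss with their primary provider".
- **Efficacy model (2.7).** Body weight and the metabolic markers "will be analyzed using a linear mixed-effects regression model for continuous outcomes". The only covariate statement is "Baseline and demographic data will be controlled for in this model". Medication change is not mentioned there, and the statement in 2.5 is neither withdrawn nor qualified.

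**The concern.** A confounder of the arm comparison has to be associated with assignment through something other than the effect of assignment. Randomisation rules that out, apart from chance, for anything that arises afterwards. A medication change at 4, 12 or 18 months can differ systematically between arms only because the arms were treated differently. In that case it lies on the path from intervention to outcome. Holding it fixed removes the part of the effect that runs through it.

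It is also likely to share causes with the outcome. The laboratory values that prompt a discussion with the provider are themselves efficacy outcomes, and both reflect an underlying disease course that is not fully measured. Conditioning on a variable affected by both the arm and that disease course opens a non-causal link between arm and outcome.

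At stake is the interpretation of the preliminary efficacy results, which the Introduction says will inform a subsequent, larger intervention. There is also a planning risk. If 2.5 is read one way and 2.7 another, the choice between adjusted and unadjusted results could be made after both have been seen.

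**Working it through.** **The plan's own figures.** No figure in the article depends on how medication changes are handled. Table A1 is a two-proportion calculation without a medication term. With 160 per arm it reproduces: power is 0.801, 0.803 and 0.806 at the tabulated 80% rates of 14.20%, 21.40% and 27.90%. The point does not rest on it.

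**Step 1: the sections side by side.** Section 2.5 names a post-randomisation variable as a confounder and as an outcome of the intervention. Section 2.7 restricts the model to baseline and demographic covariates. An analyst who follows 2.5 would control for medication change in some way; one who follows 2.7 would not. The article does not say which governs.

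**Step 2: what conditioning does.** The documents give no rate or effect for medication changes, so all inputs here are assumptions. Let A be arm (1 = intervention), M a medication start, U an unmeasured disease course and Y the outcome, where lower is better. Y is in SD units: apart from arm and medication its variance is 0.25 + 0.75 = 1.

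- P(M = 1) = 1 / (1 + exp(−(l_A + u·U))), where l_A is an arm-specific log-odds
- Y = d·A + b·M + 0.5·U + √0.75·e, with U and e standard normal
- Total effect of assignment = d + b × [P(M=1 | A=1) − P(M=1 | A=0)]
- Adjusted effect = coefficient of A when Y is regressed on A and M

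Each row is a simulation of 1,000,000 subjects. Rows 1 to 6 use d = −0.30 and b = −0.80; row 7 uses d = 0 and b = 0. A common cause means u = 1; otherwise u = 0.

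| # | Scenario | Starts, control | Starts, intervention | Total | Adjusted | Difference |
|---|---|---|---|---|---|---|
| 1 | No arm effect on M, no common cause | 15.0% | 15.0% | −0.296 | −0.297 | −0.001 |
| 2 | No arm effect on M, common cause | 18.7% | 18.8% | −0.304 | −0.303 | +0.001 |
| 3 | Fewer starts, no common cause | 20.0% | 10.0% | −0.222 | −0.302 | −0.080 |
| 4 | Fewer starts, common cause | 23.9% | 13.4% | −0.217 | −0.255 | −0.038 |
| 5 | Larger reduction, common cause | 33.1% | 13.3% | −0.142 | −0.216 | −0.074 |
| 6 | More starts, common cause | 13.4% | 23.9% | −0.383 | −0.345 | +0.038 |
| 7 | No direct and no drug effect, common cause | 33.0% | 13.5% | 0.000 | +0.083 | +0.083 |

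Check by hand, row 4: −0.30 − 0.80 × (0.134 − 0.239) = −0.216, against −0.217 simulated.

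**Step 3: reading the rows.**
- Rows 1 and 2: if the intervention does not change medication use, adjustment does no harm.
- Row 3: adjustment recovers the assumed direct effect of −0.30. That answers a different question from the total effect of −0.22.
- Rows 4 to 6: the adjusted value is neither the total effect nor the direct effect of −0.30.
- Row 7: nothing affects the outcome except U, yet adjustment produces a difference of 0.08 SD.

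**Step 4: scale.** With 320 participants split equally, the standard error of a raw arm difference in SD units is about √(2/160) = 0.112, ignoring dropout and baseline adjustment. Shifts of 0.038 to 0.083 SD are then about 0.34 to 0.74 of a standard error.

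**The case against.** The strongest reply is that the faulty model is not actually written down. Section 2.7 holds the only covariate statement and does not list medication change. Treating something as a confounder could mean a stratified or a sensitivity analysis, and details on concomitant medication are commonly left to an SAP that is not shown. This stands in part: covariate use is an inference. But 2.5 states a rule rather than leaving one out, controlling for a variable is the ordinary meaning of that rule, and an SAP that follows it would inherit the problem.

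A second reply is that a variable may be an outcome in one analysis and be accounted for in another. In an uncontrolled pre/post comparison, such as the paired *t*-test in 2.7, concurrent medication change is a genuine competing explanation. That is fair. However, 2.5 does not limit the confounder role to such comparisons, and a paired *t*-test takes no covariates.

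Third, adjustment can target a direct effect, as row 3 shows. That too is fair, but the article does not declare such a target, and the adjusted model misses it once common causes exist (rows 4 to 6).

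A reader might infer three stronger things that the documents do not support:

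- *That the efficacy estimates will certainly be biased.* This requires an arm effect on medication use. The plan entertains one but gives no evidence of it.
- *That the damage would be permanent.* Medication and outcome data are recorded separately, so the model can be refitted without the variable.
- *That the bias can be bounded.* No input is given, and different assumptions move the result in either direction. Section 2.3.1 excludes current diabetes and weight-loss drugs other than metformin, which leaves little such medication to reduce. It names no exclusion for lipid or blood-pressure drugs, so starts and changes remain possible.

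**Conclusion.** The point holds in a conditional form. Section 2.5 assigns a post-randomisation variable a role that it cannot have in the randomised comparison, and 2.7 neither repeats nor withdraws that role. If the rule is carried into the arm comparison and the intervention changes medication use, the result is no longer the total effect of assignment. With common causes of medication and outcome, it may show an effect that does not exist. If the intervention leaves medication use unchanged, there is no bias.

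Size and direction cannot be derived from the documents. The shifts of about 0.04 to 0.08 SD rest entirely on assumed start rates, drug effect and common cause; they illustrate the mechanism and are not limits.

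This should be fixed before analysis, but it is not critical. The primary aim is feasibility, analysed descriptively, and does not depend on it. The efficacy analyses concerned are secondary and described as preliminary.

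**What to change.** - In section 2.5, delete the confounder role for medication changes.
- In 2.5 or 2.7, state that the main efficacy analysis compares the randomised arms regardless of medication changes and adjusts only for baseline variables. Baseline medication, already collected, may be one of them. The covariate sentence in 2.7 is compatible with this and needs at most that clarification.
- Keep medication change as an outcome and report it by arm.
- Place any estimate that accounts for medication change in a labelled sensitivity analysis that states the question it answers. The method can be left to the analysts.

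The cost is a sentence or two and no new data. The downside is that the main estimate will include any offset from medication changes, for example if control participants start treatment more often, and it must be labelled accordingly.

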#### 2.5.1. Primary Outcomes

The primary aim of this study will be to assess the feasibility of implementing the TK-MT. Feasibility will be evaluated across common trial-level and intervention-level outcomes [48]. Trial-level feasibility outcomes are recruitment capacity and retention. Intervention-level feasibility outcomes are participant attendance, participant engagement, intervention fidelity, intervention resources, and participant and staff acceptability. The detailed data collection methods that will be used to measure feasibility outcomes are described in Table 4.

